## Abstract

**Background:**

Impulsivity is a core feature of borderline personality disorder (BPD) and is closely related to suicide risk and destructive and aggressive behaviors. Although transcranial direct current stimulation (tDCS) has shown its promising effects as an intervention to modulate impulsivity, no study has explored its potential regarding BPD.

**Methods/design:**

This is a multicenter, crossover, double-blind study comparing active versus sham tDCS (2 mA, 30 min), applied over the dorsolateral prefrontal cortex for five consecutive days in 50 BPD patients. Participants will be assessed for impulsivity, depressive symptoms, and suicide risk. The main efficacy criteria on reduction of impulsivity will be the amplitude variation of one specific evoked potential detected by electroencephalography (EEG) during the balloon analogue risk task. Baseline measures will be compared to scores obtained immediately after sessions, then 12 and 30 days later.

**Discussion:**

This study investigates the safety and effects of tDCS, which may have a significant impact on impulsivity in patients with BPD and may be useful to reduce risky behaviors.

**Trial registration:**

ClinicalTrials.gov, NCT03498937. Registered on 17 April 2018.

**Electronic supplementary material:**

The online version of this article (10.1186/s13063-019-3427-z) contains supplementary material, which is available to authorized users.

## Background

Borderline personality disorder (BPD) is characterized by a pervasive pattern of instability, affecting impulse control, emotional regulation, cognitive processing, and interpersonal relationships [1]. It is the most frequent personality disorder, with a prevalence of 1.6% in the general population and 15 to 50% in the psychiatric inpatient population [17]. Suicide is one of the leading causes of death in this population, with a rate far greater than that in the general population, estimated to be between 8 and 11% [12, 16]. In BPD, impulsivity has been shown to be closely linked to suicide risk and destructive and aggressive behavior, and it has been related to poor treatment program adherence and intense healthcare use ([2, 13, 18–20]).

Impulsivity is considered to involve failure of inhibitory control, either motor or cognitive, and deficits of the reward valuation system. From a neurobiological perspective, the prefrontal cortex is considered a critical region in the cognitive control of behaviors. Previous studies have associated hypoactivation of the dorsolateral prefrontal cortex (dlPFC) and the dorsal part of the anterior cingulate cortex to impulsivity measures in BPD [5, 15].

Despite its clinical significance, BPD remains a challenge to treat and manage. Pharmacological treatments have shown some promising effects with regard to impulsive behaviors, although results remain equivocal [14]. Efficacy of psychotherapies on BPD has been recently reviewed [4], with most trials focusing on dialectical behavior therapy and psychodynamic therapies. However, effect sizes were small and follow-up results were unstable, with no evidence of increase in treatment retention. Therefore, there is a clear need for alternative interventions that target both the cognitive control issues associated with impulsivity as well as its underlying neural dysfunction.

Transcranial direct current stimulation (tDCS) is a promising, low-risk, non-invasive neuromodulation technique that relies on the application of a weak direct current of 1–2 mA to generate regional changes in cortical excitability, which, depending on the duration and the polarity, can last for several minutes up to a few hours after stimulation [10, 11]. Due to the key role of the prefrontal cortex in cognitive control, previous studies have applied tDCS over this cortical area in healthy subjects and clinical populations (with a diagnosis of depression, attention deficit/hyperactivity disorder, or substance abuse) and have reported a significant reduction of different aspects of impulsivity, such as inhibitory control, planning, delay-discounting, and risk-taking [3, 6–9]. tDCS over the prefrontal cortex may thus be a valuable therapeutic approach that can modulate impulsivity in BPD, leading to meaningful changes in suicidal and risky behaviors.

Hence, we propose to evaluate, for the first time, the clinical benefits of tDCS on reducing impulsivity in a BPD population. The main objective will be to investigate the efficacy of 1 week of bilateral tDCS (five consecutive twice-daily sessions), applied over the dlPFC of patients with BPD, in reducing impulsivity within the following 3 weeks. This study consists of a multicenter, sham-controlled, randomized crossover double-blinded trial, comparing active tDCS versus sham tDCS. We hypothesize that the active tDCS sessions would induce a greater reduction in impulsive behavior on risk-taking tasks compared to the sham sessions.

## Methods/design

### Study setting and overview

The research will be carried out in the psychiatric departments of three clinical centers in France (in the cities of Besançon, Nancy, and Rouffach), aiming to recruit 50 patients with BPD over the course of 2 years. Potential participants will be recruited from inpatient and outpatient services in each center. After they have been provided with a complete description of the study, written informed consent will be obtained. They will be assigned to two groups, and those who start by active stimulation sessions will then be submitted to sham sessions and vice versa (Fig. 1).

**Fig. 1 Fig1:**
[figure not shown]
Study flow diagram

Baseline measures will include a clinical assessment of impulsivity, suicidal thoughts, and depression severity based on self-reports and clinician rated scales. These results will be compared to those that will be obtained immediately after the last tDCS session and then 12 and 30 days following the start of the sessions. Active and sham stimulation session outcomes will also be compared. In addition, task-based measures of behavioral and cognitive impulsivity will be administered, and data from electroencephalography (EEG) will be collected during one of the impulsivity tasks, pre- and post-tDCS administration, after 1 and 10 sessions, and 12 and 30 days later (see “Expected outcomes” section below for details).

### Inclusion criteria

Eligible patients will be invited to take part in this trial according to the following criteria: (1) male and female patients over 18 years old; (2) well-established diagnosis of BPD according to the Diagnostic and Statistical Manual of Mental Disorders, fifth edition (DSM-5) [1] and confirmed by the Structured Clinical Interview for DSM-IV-Axis II personality disorders (SCID-II); (3) absence of addictive comorbidities (except tobacco, tea, and coffee) and severe progressive neurologic and/or somatic disease.

### Exclusion criteria

Patients will be excluded if they are identified as having any of the following: (1) younger than 18 years old; (2) severe chronic psychiatric disorders, including schizophrenia, paranoia, or bipolar disorder type I and II; (3) acute serious and/or unstable medical conditions that would compromise the patient’s participation in the study, according to medical judgment; (4) use of antipsychotic and mood stabilizing treatments; (5) contraindications to tDCS, e.g., metallic foreign body in the head or medical devices implanted in the brain; (6) pregnancy; (7) concurrent participation in another trial; (8) no coverage by national health insurance; (9) measure of protection or guardianship of justice.

### Interventions

For tDCS and EEG, a wireless hybrid EEG/tDCS 8-channel neurostimulator system (StarStim®, Neuroelectrics, Barcelona, Spain) that allows for stimulation and EEG recording, with a sham and double-blind mode will be used.

Direct current will be generated by the neurostimulator and transmitted by two saline-soaked synthetic sponge electrodes. Intensity of 2 mA will be induced by two circular carbon rubber core electrodes in saline-soaked surface sponges (25 cm^2^), placed in a neoprene head cap over the dlPFC (anode position over F4 and cathode over F3, according to the EEG 10–20 International System).

In the active group, current will be delivered for 30 min, twice a day, for 5 days consecutively. For sham stimulation the procedure will be identical, except that the current will gradually ramp down to zero after 30 s, thus leading to the same initial sensations of active tDCS.

Electrophysiological signals will be recorded with the same neurostimulator system, with a sampling rate of 500 Hz. Eight dry electrodes will be placed over regions of interest for recording patients’ neuronal activity during an adapted version of the balloon analogue risk task (BART) to EEG.

Antipsychotic and mood-stabilizing treatments are forbidden during the progress of the study due to their negative impact on the action of tDCS by reducing cortical excitability.

### Outcomes

Task-based measures of behavioral and cognitive impulsivity will be administered before and after tDCS or sham stimulation. Additionally, EEG data will be collected during the BART, and resting-state EEG data will be collected pre- and post-tDCS administration to confirm engagement of the targeted brain region and to delineate the neural pathways underlying the effects of tDCS on impulsivity.

Our main efficacy criteria on reduction of impulsivity will be the amplitude variation of one specific evoked potential detected by EEG during the BART: feedback-related negativity (FRN). This reward-prediction error component is more negative when outcomes are worse than expected and more positive when they are better. The amplitude of the FRN will be compared before stimulation sessions and 5, 12, and 30 days after beginning active and/or sham tDCS.

Secondary efficacy criteria are:Changes in impulsivity (self-reported) by comparison of scores from the French version of the Barratt Impulsiveness Scale (BIS-10) obtained before the beginning of stimulation sessions and 5, 12, and 30 days after active and/or sham tDCSChanges in impulsivity (self-reported) by comparison of scores from the Urgency, Premeditation (lack of), Perseverance (lack of), Sensation Seeking, Positive Urgency Impulsive Behavior Scale (UPPS-P) obtained before the beginning of stimulation sessions and 5, 12, and 30 days after active and/or sham tDCSChanges in depression severity (clinician-rated) by comparison of scores from the Hamilton Depression Rating Scale (HDRS) obtained before the beginning of stimulation sessions and 5, 12, and 30 days after active and/or sham tDCSChanges in depression severity (clinician-rated) by comparison of scores from the Montgomery and Asberg Depression Rating Scale (MADRS) obtained before the beginning of stimulation sessions and 5, 12, and 30 days after active and/or sham tDCSChanges in depression severity (self-reported) by comparison of scores from the 16-item Quick Inventory of Depressive Symptomatology (QIDS-SR16) obtained before the beginning of stimulation sessions and 5, 12, and 30 days after active and/or sham tDCSChanges in suicidal thoughts (clinician-rated) by comparison of scores from the Columbia-Suicide Severity Rating Scale (C-SSRS) obtained before the beginning of stimulation sessions and 5, 12, and 30 days after active and/or sham tDCSChanges in impulsivity (behavioral assessment of inhibitory control) by comparison of scores from the experimental Go/No-Go and Stroop tasks obtained before the beginning of stimulation sessions and 5, 12, and 30 days after active and/or sham tDCS

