**Fig. 2 Fig2:**
[figure not shown]
Randomized cross-over design for TIMBER (Standard Protocol Items: Recommendations for Interventional Trials (SPIRIT) figure)

The second phase will correspond to both inclusion of volunteers and the period of the tDCS sessions. All volunteers will have to sign the informed consent. Diagnosis will be established by an experienced psychiatrist, in accordance with DSM-5 criteria and confirmation by the SCID-II, as stated in the inclusion criteria section. Clinical assessment will be performed and behavioral baseline scores will be collected. Following completion of baseline clinical measures, subjects will be randomly assigned using a computer-generated randomization list with the information stored on a centralized computer to receive either active or sham tDCS. Predefined codes assigned to either real or sham stimulation will be used by trained staff and health care professionals to start the stimulator, allowing a double-blind study design. The first tDCS session will be delivered on a Monday. Two daily sessions will be performed during the following days up to Friday. The clinical and behavioral assessment will be performed once the last tDCS session has been delivered (day 5) and then 12 (day 12) and 30 days (day 30) following the start of the sessions.

Following the last assessment, subjects who underwent active stimulation sessions will then be submitted to sham sessions and vice versa (third phase). Then, once again, baseline measures will be performed before new sessions start, followed by evaluation immediately after their end and then 12 and 30 days after the start.

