### Sample size

Our primary efficacy outcome concerns changes in impulsivity by means of assessment of risk in conjunction with EEG measures. In this context, a sample size calculation based on an expected difference of 2 mV between the variation of amplitude of the FRN recorded by EEG during the BART, with a standard deviation for paired-differences of 3 and with an autocorrelation of 10% between measures in the same subject, was performed. Considering a significance level of 5%, a power of 90%, and a drop-out rate of 10% of patients, 50 patients should be included to meet the objectives of the study.

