### Data management and statistical analyses

Collected information will be stored in physical files (Case Report Files (CRFs)), registered under each participant’s randomization code to respect confidentiality at all times. All researchers and trained staff called upon to collaborate in the tests are bound to secrecy. An anonymous electronic database (eCRFs) will be created, with controlled access, on the platform CleanWEB™, allowing multicenter data analysis.

All randomized patients will be used for the efficacy analyses. Qualitative variables will be described in terms of effective, absolute, and relative frequencies for each modality. Quantitative variables will be described in terms of minimum and maximum, quartiles, means, and standard deviations.

Comparison between active and sham stimulation will be based on the Student’s *t*-test for quantitative variables and the Wilcoxon test for semi-quantitative variables. The Student’s *t*-test or the Mann-Whitney test will be used for comparison of amplitude variation detected by the EEG. Analyses will be performed using Stata Software release 10.1 (StataCorp, Collège Station, TX, USA). No interim analyses will be performed.

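### Comparing raw FRN change between active and sham fixes the baseline slope at 1; adjusting for the period baselines already collected would be more precise, by an amount that depends on a correlation the article does not give

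*Protocol article*

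**What the plan says.** All references are to the protocol article.

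- **Outcomes** defines the primary variable as a change from baseline: the main criterion "will be the amplitude variation of one specific evoked potential detected by EEG during the BART", the component being feedback-related negativity (FRN). The times are also given: "The amplitude of the FRN will be compared before stimulation sessions and 5, 12, and 30 days after beginning active and/or sham tDCS".
- **Data management and statistical analyses** names the test: "The Student’s *t*-test or the Mann-Whitney test will be used for comparison of amplitude variation detected by the EEG". No baseline covariate is mentioned, and neither test can carry one.
- **Sample size** uses the same variable: "an expected difference of 2 mV between the variation of amplitude of the FRN recorded by EEG during the BART". The SD of 3 is labelled as one for paired differences. An "autocorrelation of 10% between measures in the same subject" is assumed as well, together with 5% significance, 90% power, 10% drop-out and 50 patients.
- **Study procedure** states that before the second period "once again, baseline measures will be performed before new sessions start". Each patient therefore has a baseline for the active period and another for the sham period.
- The secondary criteria in **Outcomes** are also framed as changes in scores from before stimulation.

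**The concern.** A change score is a baseline adjustment with the slope set to 1 in advance. If the true slope is below 1, too much of the baseline is subtracted and its noise enters the treatment contrast. Estimating the slope avoids this and needs no data beyond what the trial already collects. What is at stake is precision on the primary outcome, and on each secondary scale analysed as change. The planning values are guesses for a trial that its Discussion calls a pilot and the first of its kind in this population. Spare precision would protect against a larger SD or more drop-out than planned.

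**Working it through.** **1. Reproducing the plan's figure.** Inputs from Sample size: difference 2, SD 3, correlation 0.10, alpha 5%, power 90%, drop-out 10%. Two-sided testing and a paired comparison are my assumptions; the article states neither explicitly.

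- If 3 is the SD of each of the two quantities being differenced, the SD of the difference is √(2 × 9 × (1 − 0.10)) = √16.2 = 4.02.
- A paired t-test (noncentral t) then needs 45 completers, with power 90.3%, and 45/0.9 = 50. This matches the plan.
- If 3 is itself the SD of the paired difference, as the text labels it, the result is 26 completers and 29 patients. The label is a separate matter and does not affect the variance ratio below.

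On the reading that reproduces 50, the 0.10 links the active quantity to the sham quantity. It need not be the correlation between a baseline and its own post-treatment value.

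**2. Variance of the two analyses.** Let D_Y be a patient's active-minus-sham difference in post-treatment FRN at one assessment time, D_B the matching difference in period baselines, and r their correlation. Assume both have the same variance V.

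- Change score: Var(D_Y − D_B) = 2V(1 − r).
- Adjusted: Var(D_Y given D_B) = V(1 − r²).
- Ratio, adjusted to change: V(1 − r²) / [2V(1 − r)] = (1 + r)/2.

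If every between-period correlation equals ρ_b and the within-period pre-post correlation is ρ_w, then r = (ρ_w − ρ_b)/(1 − ρ_b). When all measures within a patient correlate equally, r = 0 and the variance is halved whatever the common correlation is. When a post-treatment value follows its own baseline more closely than the other period's baseline, r > 0 and the gain is smaller. For example, ρ_w = 0.7 with ρ_b = 0.5 gives r = 0.2/0.5 = 0.4 and a ratio of 0.70.

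**3. Consequence for power.** Start from the contrast variance of 16.2, difference 2, 45 completers, two-sided 5%. The values of r are illustrations.

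| r | Factor (1+r)/2 | Variance | SD | Power |
|---|---|---|---|---|
| change score | 1 | 16.20 | 4.02 | 90.3% |
| 0 | 0.50 | 8.10 | 2.85 | 99.6% |
| 0.3 | 0.65 | 10.53 | 3.24 | 98.1% |
| 0.5 | 0.75 | 12.15 | 3.49 | 96.4% |
| 0.7 | 0.85 | 13.77 | 3.71 | 94.2% |

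These use 44 degrees of freedom. With 42, to allow for the covariate and period, no power in the table falls by more than 0.1 percentage point.

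**4. Carryover.** Suppose active treatment in period 1 leaves an effect λ on period 2. It then touches only the active-first sequence, half the patients. With equal variances the adjusted slope is r.

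- λ unchanged from the second baseline through period 2: in active-first patients D_Y and D_B both shift by −λ. The change score is unbiased. The adjusted estimate is biased by −(1 − r)λ/2.
- λ present at the second baseline and gone by the post-treatment measure: only D_B shifts. The change score is biased by +λ/2. The adjusted estimate is biased by +rλ/2.

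With a true effect of 2, λ = 1 and r = 0, the first case gives 2.0 for change and 1.5 for adjusted. The second gives 2.5 and 2.0. Simulation agreed (1.99 and 1.49; 2.50 and 2.00).

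**The case against.** Four points can be made for the plan.

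*The size is unknown.* A reader might infer from the 10% autocorrelation that subtracting a barely correlated baseline doubles the error variance. The article does not support this. The 0.10 that reproduces 50 patients applies to the active-sham pair, and no pre-post correlation is given. A halving needs r = 0, which is nowhere stated. A post-treatment value taken days after its own baseline, with the other period's baseline a month or more away, plausibly gives r > 0. This objection stands: the gain must be shown as a range. For the secondary scales no size can be given at all.

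*The trial may not be short of power.* A reader might also infer that power is really 87%. That follows only if each change has SD 3 and all four measures correlate equally, which makes the two changes uncorrelated (contrast SD 3√2 = 4.24). It is not the plan's own figure. On the reading that reproduces 50, the unadjusted analysis has its stated 90%. This stands too.

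*Adjustment is not always better.* Period 2 follows the day-30 assessment with no further interval stated, and the Background expects an effect over the three weeks after the treatment week. Persistent carryover biases the adjusted estimate and spares the change score; carryover that fades does the reverse. This defeats any claim that adjustment is never worse. It calls for a sensitivity analysis and is no reason to drop a standard adjustment.

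*Covariates are often left to the full protocol or analysis plan.* True in general. Here, though, the article itself fixes both the change variable and tests that take no covariate, so the choice is open to comment.

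**Conclusion.** The point holds as one of efficiency. The planned comparison of raw FRN change gives up precision that the two period baselines could supply. Given equal pre and post variances and no carryover, adjustment cuts the contrast variance by 50%, 35%, 25% or 15% at r = 0, 0.3, 0.5 or 0.7. Power on the plan's reproducing assumptions rises from 90% to between about 99.6% and 94% over that range. The value of r is an assumption throughout, as are two-sided testing and a paired comparison. Nothing here shows bias in the planned analysis, inflation of the type I error or an inadequate sample of 50.

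**What to change.** In Data management and statistical analyses, replace the test of FRN variation as the primary analysis. Analyse the within-patient active-sham difference in post-treatment FRN amplitude, with the difference between the two period baselines as covariate and period in the model. An equivalent form is a crossover mixed model for post-treatment FRN with the period-specific baseline and the patient's mean baseline as covariates. Treat the secondary scales analysed as change (BIS-10, UPPS-P, HDRS, MADRS, QIDS-SR16, Go/No-Go, Stroop) the same way. Keep the change-score comparison as a named sensitivity analysis, and state the reason: the two estimates respond in opposite ways to persistent and to fading carryover, so a clear gap between them is a warning.

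Cost: no new visits, patients or data. One or two degrees of freedom are spent, and the primary estimate becomes sensitive to carryover that persists through period 2. It replaces a simple test with a model, so the wording should be settled before unblinding.

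### The primary FRN endpoint is compared at days 5, 12 and 30 with no primary visit or combined test named, so the 5% error rate and 90% power belong to no defined test

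*Protocol article*

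**What the plan says.** The Outcomes section of the protocol article names one primary measure: "Our main efficacy criteria on reduction of impulsivity will be the amplitude variation of one specific evoked potential detected by EEG during the BART", the component being the FRN. It then gives the timing: "The amplitude of the FRN will be compared before stimulation sessions and 5, 12, and 30 days after beginning active and/or sham tDCS". That makes three post-baseline visits, listed on an equal footing.

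The Sample size section works with a single effect: "expected difference of 2 mV between the variation of amplitude of the FRN recorded by EEG during the BART". Its assumption about variability reads: "with a standard deviation for paired-differences of 3 and with an autocorrelation of 10% between measures in the same subject". The error rates and attrition are set in one clause: "Considering a significance level of 5%, a power of 90%, and a drop-out rate of 10% of patients". The result is an enrolment of 50. The section ties the difference to no visit.

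The Data management and statistical analyses section plans a Student's t-test or a Mann-Whitney test for the EEG amplitude variation. It gives no visit, no summary over visits and no rule for several tests.

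Two other places bear on timing. The main objective in the Background looks for an effect "in reducing impulsivity within the following 3 weeks". Study setting and overview lists EEG collection "pre- and post-tDCS administration, after 1 and 10 sessions, and 12 and 30 days later" and refers the reader to the outcomes section for details.

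**The concern.** A primary endpoint consists of a measure, a time and a comparison. Here the measure is fixed and the comparison can be inferred, but the time is left as three alternatives. A 5% error rate and 90% power are properties of one specified test. With three candidates and no rule for choosing or combining them, the visit could be chosen after the data are seen, and the trial could then report success at a false-positive rate well above the one stated.

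The phrase about active and/or sham stimulation adds some looseness, since it could also cover pre-post comparisons within one condition. Such a comparison cannot separate stimulation from repeated exposure to the task or from regression to the mean.

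**Working it through.** **Inputs.** From the Sample size section: difference 2, SD 3, correlation 0.10, alpha 5%, power 90%, dropout 10%, N = 50. From the Outcomes section: three post-baseline visits. Not given: whether the test is two-sided, and the correlation between the visit contrasts.

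**Step 1: reproduce the stated sample size.** Take 3 as the SD of each measure, with correlation 0.10:

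- SD of the paired difference = 3 × √(2 × (1 − 0.10)) = 4.025.
- A two-sided paired t-test at 5% with 90% power for a difference of 2 needs 45 evaluable patients (noncentral t; power 90.3%).
- 45 / (1 − 0.10) = 50, which matches.

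Reading 3 as the text describes it, as the SD of paired differences, gives 26 evaluable and 26 / 0.90 = 28.9, so 29 enrolled. A one-sided test with SD 4.025 gives 37, then 42. The stated N therefore fits one two-sided paired contrast. It contains no allowance for three.

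**Step 2: error rate if any of the three visits may count.** For independent tests this is 1 − 0.95³ = 14.3%. For correlated tests it was simulated: three two-sided paired t-tests, 45 patients, 400,000 replicates, equal correlation r between the visit contrasts.

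| r | Chance of at least one false positive |
|---|---|
| 0.1 | 14.2% |
| 0.3 | 13.7% |
| 0.5 | about 12.5% |
| 0.7 | 11.0% |
| 0.8 | 10.0% |
| 0.9 | 8.4% |

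**Step 3: a plausible r.** Let every measure have variance σ² and every pair of measures in a period have correlation ρ. The change from baseline then has variance 2σ²(1 − ρ). Two changes sharing that baseline have covariance ρσ² − ρσ² − ρσ² + σ² = σ²(1 − ρ). Their correlation is σ²(1 − ρ) / 2σ²(1 − ρ) = 0.5, whatever ρ is. If the correlations between active-period and sham-period measures are also all equal, they cancel in the covariance of the changes, and the active-minus-sham contrasts keep r = 0.5. The corresponding error rate is about 12.5%.

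**Step 4: cost of keeping all three visits as primary.** Bonferroni gives 0.05 / 3 = 0.0167 per visit.

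- SD of the difference 4.025, the reading that reproduces N = 50: power per visit with 45 evaluable falls from 90.3% to 79.7%. Restoring 90% needs 58 evaluable, and 58 / 0.90 = 64.4, so 65 enrolled.
- SD of the difference 3, as printed: power falls only from 99.2% to 97.3%.

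**Step 5: the objective's window against the visits.** The last session is on day 5. Three weeks after it is day 5 + 21 = day 26. Day 12 is 7 days after the last session and lies inside the window. Day 30 is 30 − 5 = 25 days after it and lies outside.

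**The case against.** The strongest counter-case is that the article condenses a fuller protocol, calls the trial a pilot, and leaves test hierarchy to documents that are not shown. Multiplicity detail often does sit elsewhere. But the time point is part of the primary endpoint. The article does not leave timing out: it gives three times for the primary measure and sizes the trial for one difference. The pilot label does not remove the point either, since the same article states an efficacy objective and a 90%-power calculation.

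Several limits on the point do stand:

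- A reader might infer that the trial has a 14% false-positive rate. The article states no any-visit success rule, and 14% is close to the value for independent tests, which repeated measures on the same patients would not reach if, as expected, they are appreciably correlated.
- A reader might count the EEG recording after the first session as a fourth primary test. It appears only in a list of collection times; the Outcomes section names days 5, 12 and 30 for the FRN.
- A reader might take the and/or wording to mean that a pre-post change within one condition could carry the efficacy claim. The hypothesis in the Background and the statistical section both point to active versus sham, so the type of comparison can be inferred. The visit cannot.
- A reader might conclude that the three-week objective matches none of the visits. Only day 30 falls outside it.
- A reader might prefer day 5 as the visit safest from carry-over. That does not follow: in the second period, day 5 is the post-baseline visit closest in time to the first-period stimulation.

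**Conclusion.** The point holds in conditional form. The primary measure is compared at three visits, none is primary, no combined test is given, and the sample size fits a single contrast. If significance at any visit can count, the false-positive risk is about 8% to 14%, or roughly 1.7 to 2.9 times the nominal 5% (8.4 / 5 = 1.7; 14.3 / 5 = 2.9), with about 12.5% the most plausible value. The range rests on an assumed between-visit correlation of up to 0.9; the 12.5% rests on equally correlated measures and a shared baseline. The loss of power from 90% to 80% under Bonferroni is not a general result: it applies only if 3 is the SD of each measure with correlation 0.10.

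**What to change.** Before unblinding, define one primary contrast: active minus sham in FRN change from period baseline. Either of two forms would do.

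- **One named visit.** Day 5 is defensible, because the Background describes after-effects lasting from minutes to a few hours. With 45 evaluable patients the power is 90.3% under the reading that reproduces N = 50.
- **One combined contrast**, such as the mean over visits chosen to fit the stated objective. With three visits and r = 0.5, the SD of the mean is √((1 + 2 × 0.5) / 3) = 0.816 times that of one visit. An average difference of 0.816 × 2 = 1.63 would then keep the same power; an effect that fades below this would lose power.

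Test the remaining visits, or the single visits behind a combined contrast, in fixed order as secondary. Treat pre-post comparisons within a condition as descriptive. Reword the three-week objective or state how day 30 relates to it.

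Alpha stays at 5% and enrolment at 50. The cost is a modification to an approved protocol in a trial that the article describes as recruiting, and an effect seen only at another visit becomes secondary evidence.
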